#### Exclusion criteria

Participants meeting any of the following conditions will be excluded:Cognitive impairment or psychiatric disorders such as depression. > 5 kg weight fluctuation within 3 months prior to enrollmentCurrently enrolled in another weight-loss program or have taken medications that affect metabolism or body weight (such as glucocorticoids or antibiotics) in the past 3 months.Diagnosed with any of the following conditions: diabetes; impaired liver function or active liver disease; impaired renal function or chronic kidney disease; active malignancy or history of malignancy within the past 5 years; malabsorption, functional gastrointestinal disorders; uncontrolled hyponatremia; hyperthyroidism; hypothyroidism; Cushing’s syndrome; eating disorders such as anorexia nervosa or bulimia nervosa; or any other diseases affecting body weight.oDefinition of impaired liver function: alanine aminotransferase (ALT) and/or aspartate aminotransferase (AST) levels > 3 times the upper limit of the age- and sex-specific reference range [39].oDefinition of impaired renal function: serum creatinine levels > the upper limit of the age- and sex-specific normal range [39].History of food allergies or bariatric surgery; serious gastrointestinal disorders or gastrointestinal surgery within 12 months prior to randomization; smoking; known or suspected alcohol or recreational drug abuse; HIV infection; immunodeficiency; or any other condition that makes the participant unsuitable for the study.Any other condition deemed inappropriate by investigators

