#### Withdrawal or discontinuation criteria

Participant involvement in the study will be terminated under any of the following conditions:Emergence of serious adverse events (related or unrelated to intervention) including diseases requiring excluded medications (e.g., systemic glucocorticoids), serious infectious diseases and any life-threatening conditionsParticipant or legal guardian requests to withdraw consent, or the participant is unwilling to comply with the intervention protocol, or other unforeseen reasons.

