Participants in the control group will receive standard clinical dietary advice for weight management based on the Nutritional Guidelines for Weight Management of School-Aged Children [35], which include recommendations on energy intake and healthy dietary patterns. The mode and frequency of feedback and supervision will be consistent with those of the intervention group. Both groups will receive regular health education on lifestyle topics, including balanced nutrition, physical activity, and sleep hygiene. Comprehensive assessments, including food frequency questionnaires (FFQ), 24-h dietary recalls, anthropometric measurements, body composition analysis, laboratory tests, and relevant questionnaires, will be conducted at baseline (week 0), week 12, and week 24. During the study period, participants will be asked not to engage in any additional weight-loss interventions, including other dietary programs, medications, or structured exercise regimens outside of their usual activities. Routine pediatric care and non-weight-related treatments will be allowed.

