#### Secondary outcomes

Body weight and body composition indicators:BMIz: Between-group differences at week 24; within-group changes from baseline at weeks 12 and 24.Degree of reduction in %BMI_95_ (≥ 5%, ≥ 10%, and ≥ 15%), waist-to-height ratio, and body composition parameters (fat mass index [FMI], fat-free mass index [FFMI], visceral fat area, body fat percentage): between-group and within-group changes at weeks 12 and 24.Growth and developmental indicators:Height, Tanner stage, annual growth velocity (GV), and height SDS changes from baseline, with between-group comparisons at weeks 12 and 24.GV (cm/year) = 12 * (current height – previous height)/(visit interval in months).Height SDS is calculated based on data from the 2005 Chinese National Growth Survey in nine cities [41]: Height SDS = (height at assessment time − mean height for same age/gender group)/standard deviation of height for same age/gender group).IGF-1 changes from baseline and between-group comparisons at week 24.Cardiometabolic risk factors and serum biochemical indicators:Blood pressure; serum biochemical indicators (high-sensitivity C-reactive protein, liver function, renal function, uric acid); lipid profile (total triglycerides, HDL-C, LDL-C); blood glucose at 0, 60, and 120 min during the oral glucose tolerance test (OGTT); insulin release test (IRT); area under the curve (AUC) for OGTT and IRT; homeostasis model assessment of insulin resistance (HOMA-IR) and β-cell function (HOMA-B): between-group and within-group changes at weeks 12 and 24Dietary and psychobehavioral parameters:Dietary quality (dietary balance index, dietary inflammatory index, etc.), dietary patterns, sleep, anxiety levels, and physical activity: between-group and within-group changes at weeks 12 and 24.Adverse events (AEs):AEs will be systematically monitored and recorded throughout the trial. Expected AEs in this low-risk intervention are mild.Between-group differences in the incidence of all AEs at weeks 12 and 24.

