### Adverse events and safety monitoring

No formal interim analyses or stopping guidelines are planned; all data will be analyzed post-follow-up. However, the principal investigator (PI) will suspend the trial immediately if ≥ 3 intervention-related serious AEs (SAEs) occur in one group, with final termination requiring PI and IRB consensus. This ensures participant safety while aligning with predefined secondary endpoints for AE incidence.

An adverse event (AE) is defined as any unfavorable sign, symptom, or medical condition that arises after the initiation of the study intervention. Pre-existing medical conditions or diseases will only be considered AEs if they worsen after the start of the intervention. Unchanged pre-existing conditions will not be classified as AEs. Abnormal laboratory findings will not be considered AEs unless deemed clinically significant by the investigator.

At each clinical visit, the investigator (or a designated staff member) will assess whether any AEs have occurred. If a participant is unable to continue in the study due to an AE or other unavoidable reason, the intervention will be discontinued. Reasons for discontinuation may include gastrointestinal symptoms or growth and developmental issues that, in the opinion of the physician, warrant termination of the intervention.

All AEs will be evaluated and managed by the participant’s physician and monitored until resolution to ensure participant safety. AEs will be systematically documented according to standardized procedures. The incidence of AEs is predefined as a secondary endpoint to support a comprehensive benefit-risk assessment of the intervention.

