### Quality control and data management

Data will be collected using paper Case Record Forms (CRFs). Prior to participant enrollment, all study personnel will receive standardized training to ensure proper understanding of study procedures and data recording requirements. Data will be recorded by trained investigators in real time, followed by independent double-checking by two individuals to ensure completeness and logical consistency of the forms. Data entry will be performed using a double-entry system. Upon completion, consistency checks will be conducted. Any discrepancies or abnormal values will be traced back to the original records for verification and correction. All participants will be identified using unique study codes. The linkage between personal information and study codes will be stored separately, accessible only to authorized research staff for necessary identification. All paper-based data will be securely stored in designated cabinets, with no access granted to unauthorized personnel. The hospital’s Ethics Committee will oversee the data collection and management process to ensure compliance with ethical guidelines and data protection requirements.

To promote participant retention and adherence to the follow-up schedule, regular reminders (e.g., phone calls or text messages) will be provided before each study visit. Participants and their guardians will receive educational support and periodic feedback regarding progress. Concurrent health education sessions during visits will reinforce engagement and study goal understanding. For participants who withdraw or deviate from the intervention protocol, efforts will be made to collect primary and secondary outcome data at all available time points, particularly at the 12-week and 24-week assessments.

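### The withdrawal rule makes need for an entry-excluded drug a serious adverse event that ends study involvement, which conflicts with the protocol's own text on permitted care, stopping the diet and outcome follow-up

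*Protocol article*

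**What the plan says.** Five parts of the protocol article bear on a child who falls ill after randomisation.

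- **Withdrawal or discontinuation criteria.** The opening is "Participant involvement in the study will be terminated under any of the following conditions". The first condition is "Emergence of serious adverse events (related or unrelated to intervention) including diseases requiring excluded medications (e.g., systemic glucocorticoids"). The same sentence goes on to list serious infections and life-threatening states as separate items.
- **Exclusion criteria.** Children are kept out if they "have taken medications that affect metabolism or body weight (such as glucocorticoids or antibiotics) in the past 3 months".
- **Intervention measures.** After asking families to avoid other weight-loss interventions, the section adds: "Routine pediatric care and non-weight-related treatments will be allowed".
- **Adverse events and safety monitoring.** An adverse event is "any unfavorable sign, symptom, or medical condition that arises after the initiation of the study intervention". When a participant cannot go on because of one, the stated consequence is that the intervention stops. The trial is suspended if three or more "intervention-related serious AEs (SAEs) occur in one group".
- **Quality control and data management.** For participants who withdraw or deviate, "efforts will be made to collect primary and secondary outcome data at all available time points, particularly at the 12-week and 24-week assessments".

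The safety endpoint, under Secondary outcomes, is "Between-group differences in the incidence of all AEs at weeks 12 and 24". The Statistical analysis section declares an intention-to-treat analysis using mixed-effects models.

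**The concern.** A drug list written to screen children at entry appears to be reused after randomisation for two other purposes: to decide what counts as serious, and to decide who leaves the study. Need for a drug is not a measure of seriousness, and antibiotics are on the list. The withdrawal sentence applies whether or not the event is related to the intervention.

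Two things are at stake. The first is the meaning of SAE. The article defines an adverse event but gives no separate definition of a serious one, so the withdrawal sentence is the only text that says what the term includes. The suspension rule uses the same term, and the Oversight and monitoring section provides no data monitoring or adjudication committee to settle its meaning. The second is follow-up. Ending a child's study involvement for an unrelated illness threatens the week-12 BMI z-score that the primary analysis needs from every randomised child.

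**Working it through.** **Step 1: what the excluded medications are.** The withdrawal criteria give one example, systemic glucocorticoids. The exclusion criteria are the only other place where glucocorticoids are named, and they name antibiotics beside them. The other medication restriction, in Intervention measures, concerns weight-loss treatment and does not fit the example. The natural referent is therefore the entry list, which includes antibiotics.

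**Step 2: apply each section to one case.** Take a child with a mild infection who is given a short antibiotic course in week 6.

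| Section | Consequence as written |
|---|---|
| Withdrawal criteria, excluded-medication item | SAE; study involvement ends |
| Withdrawal criteria, infection item | Not met, because the infection is not serious |
| Intervention measures | The treatment is allowed; no exception for antibiotics |
| Adverse events and safety monitoring | Adverse event; if the child cannot continue, the intervention stops |
| Quality control and data management | Week-12 and week-24 outcomes are sought if the child withdraws or deviates |
| Statistical analysis | The child is analysed as randomised |

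The first row does not agree with the others. Within the withdrawal sentence, one item selects infections by seriousness and another selects diseases by drug.

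**Step 3: the safety endpoint.** It counts all adverse events. Under the article's definition the infection is one event whether or not it is called serious, so the endpoint does not change. Only a separate SAE tally would. The suspension rule counts only intervention-related SAEs, so an unrelated infection does not add to it.

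**Step 4: the primary endpoint.** No figure in the article depends on the antibiotic rule, and no rate of antibiotic use is given. The loss therefore cannot be computed. The cost of any given loss can be shown, for illustration only.

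- Inputs (Sample size estimation): difference 0.14, SD 0.28, two-sided 0.05, power 85%, dropout 20%, 82 per group.
- The plan's figure: n per group = 2 × (1.960 + 1.036)² × (0.28/0.14)² = 71.8, rounded up to 72. Then 72/0.8 = 90 per group, 180 in all, against the stated 164. The stated total does not reproduce from its inputs; that is a separate matter.
- At 82 per group with 20% dropout: 82 × 0.8 = 65.6 evaluable. Power = Φ(0.5 × √(65.6/2) − 1.960) = Φ(0.904) = 0.817.
- Assumed extra loss of week-12 data, as a share of those randomised, on top of the 20%:

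| Extra loss (assumed) | Evaluable per group | Power |
|---|---|---|
| 0% | 65.6 | 0.817 |
| 5% | 61.5 | 0.792 |
| 10% | 57.4 | 0.764 |
| 20% | 49.2 | 0.698 |
| 30% | 41.0 | 0.619 |

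These rows use a simple two-group comparison by normal approximation and suppose that the lost outcomes are not recovered. If outcomes are collected as the data management section intends, the first row applies.

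**The case against.** The withdrawal sentence never names antibiotics. Its head term is serious adverse events, its example is systemic glucocorticoids, and its separate item for serious infections would be largely redundant if every antibiotic-treated infection already qualified. The entry list is a three-month look-back and is not stated to apply after randomisation. The sentence allowing routine care qualifies a ban on other weight-loss treatment and does not say who stays in the study. A condensed article may also leave the full SAE definition to the full protocol.

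Much of this stands, and it makes a narrower reading plausible. It does not remove the problem. An illustrative example does not take antibiotics off the list, and the narrower reading has to be inferred. The point also does not rest on missing detail: the rule is stated, and as stated it conflicts with other stated text.

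A reader might infer more than the document supports:

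- **That the safety endpoint is inflated.** It counts all adverse events, so the infection counts once either way.
- **That week-12 data are lost.** The data management section plans to seek them. It promises efforts, however, and speaks of participants who withdraw or deviate, so a child removed by the investigators is not plainly covered. At risk is the right description.
- **That a known number of children would be removed.** Any such count needs an antibiotic rate that the article does not give, and the literal reading applied to every course.
- **That sites would differ, or that the arms would.** The trial is single-centre, so any inconsistency would be between investigators. Those delivering the intervention are unblinded, so a difference by arm is possible, but nothing in the article shows one.

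**Conclusion.** The concern holds as a contradiction in the stated rules. Read as written, the withdrawal criteria turn need for an entry-excluded drug into an SAE and end the child's study involvement. That conflicts with the allowance for routine care and with the limit to serious infections in the same sentence. It also conflicts with the sections that stop only the intervention, continue to seek outcomes and analyse by intention to treat. The conclusion rests on one assumption, that the excluded medications in the withdrawal criteria are those of the exclusion criteria; no other list in the article fits.

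What is affected is the classification of events as serious and the security of week-12 and week-24 follow-up. The size cannot be derived from the article. If the planned outcome collection is carried out, the extra loss is near zero. If it is not, the illustration shows about 2.5 to 3 points of power for each of the first two extra 5 points of missing week-12 data, starting from about 0.82.

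**What to change.** Reconcile the exclusion criteria, withdrawal criteria, Intervention measures, safety and data management sections:

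1. Classify an event as an SAE by its seriousness, not by whether an entry-excluded drug is used.
2. Record use of such drugs after randomisation as concomitant medication.
3. State in the withdrawal criteria that stopping the intervention does not end outcome follow-up, so that week-12 and week-24 BMI z-scores are collected as the data management section intends. Withdrawal of consent remains a separate matter.

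Which treatments lead to stopping the diet, and which count as routine care, are for the sponsor to settle; the sections need to give one consistent answer.

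The cost is a wording amendment and one line on the case record form, with no added visits or staff.

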### Randomization and allocation

Eligible participants will be randomized 1:1 to the ASER or control group using centralized, computer-assisted minimization with allocation concealment, balancing age (8–9 years vs. 10–11 years), sex (male vs. female), and baseline BMI *z*-score category (mild: + 1.645 ≤ z < + 2.5; moderate: + 2.5 ≤ z < + 3.0; severe: z ≥ + 3.0). To avoid treatment contamination, related participants from the same family will be allocated to the same intervention group. Randomization will be implemented by an independent statistician via a secure system; site investigators will enroll participants, submit baseline stratification variables, and receive the assignment, with the allocation sequence concealed from site staff until assignment. Due to the nature of the intervention, blinding of participants and intervention implementers is not feasible. However, health education physicians, data collectors, and outcome assessors/statisticians will remain blinded to group assignments throughout the study.

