### Recruitment and informed consent

Participants will be recruited from eligible children with obesity attending non-boarding public primary schools in urban areas of Nanning. Recruitment is expected to take place from October 2025 through April 2026. All participants and their legal guardians will receive detailed information about the study procedures, potential benefits, and risks. Written informed consent will be obtained from legal guardians. In addition, assent will be obtained from children aged 8 years and older who demonstrate adequate comprehension. This study was approved by the Medical Ethics Committee of the First Affiliated Hospital of Guangxi Medical University (Approval No.: 2025-K0254).

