### Statistical analysis

Data analysis will follow the intention-to-treat (ITT) principle and will be conducted under blinded conditions. For the primary endpoint (between-group difference in BMI *z*-score change at week 12) and secondary endpoints involving continuous variables (BMI *z*-scores, waist-to-height ratios, body composition parameters, cardiometabolic markers, and psychobehavioral measures, etc.) at weeks 12 and 24, longitudinal changes will be assessed using mixed-effects models. These models will account for within-participant correlations and missing data. A time-by-group interaction term will be included to evaluate whether there are significant differences in weight reduction between the study groups. The models will be adjusted for stratification factors (age, sex, and baseline BMI *z*-score) and corresponding baseline values to control for any potential systematic group differences at baseline.

Continuous variables will be compared using independent-sample *t*-tests or Mann–Whitney *U* tests, as appropriate. Categorical outcomes, including the proportions achieving predefined reductions in %BMI95 (≥ 5%, ≥ 10%, ≥ 15%) and AE incidence, will be analyzed using chi-square tests and logistic regression. Sensitivity analyses will be conducted to test the robustness of the results. A post hoc analysis will compare adherers and non-adherers, with adherence defined as attendance at ≥ 50% of scheduled visits during the 24-week study period. Exploratory dietary adherence will be defined at the participant level as not exceeding the group-specific upper limit at ≥ 50% of available post-baseline recalls. Participants with fewer than two post-baseline recalls will be considered not classifiable for dietary adherence analyses. Statistical significance will be set at a two-tailed *P*-value of < 0.05. All analyses will be performed using SPSS and R software.

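### Relatives share one arm, but the stated analysis names no family clustering, and concealment fails for any sibling who enters after the family's arm is known

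*Protocol article*

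**What the plan says.** All of the allocation text is in the protocol article, Randomization and allocation:

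- Allocation is described for individual children: "Eligible participants will be randomized 1:1 to the ASER or control group", by centralized minimization on age, sex and baseline BMI z-score category.
- Relatives are an exception, made to prevent contamination: "related participants from the same family will be allocated to the same intervention group". The section does not say whether siblings are assigned together or one after another.
- Concealment is stated without any exception: "with the allocation sequence concealed from site staff until assignment".
- The people who enrol also learn the arm: "site investigators will enroll participants, submit baseline stratification variables, and receive the assignment". The trial is open-label, since "blinding of participants and intervention implementers is not feasible".

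Recruitment and informed consent gives the time frame: "Recruitment is expected to take place from October 2025 through April 2026". Trial status puts the start later, in late December 2025 or early January 2026. If the April end stands, that still leaves several months.

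Statistical analysis describes mixed-effects models for the primary endpoint and the other continuous outcomes: "These models will account for within-participant correlations and missing data". On covariates it says "The models will be adjusted for stratification factors (age, sex, and baseline BMI" z-score), together with the baseline value of each outcome. It also lists two-sample t-tests or Mann–Whitney tests for continuous variables, and chi-square tests and logistic regression for categorical outcomes. It mentions no family term, no clustered errors and no limit of one child per family. Sample size estimation contains no design effect.

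**The concern.** The same-family rule turns each participating sibling group into a small cluster that lies wholly in one arm. Siblings share a household and caregivers. Under Intervention measures, it is the caregivers who receive the teaching, prepare and weigh the evening food and send in the records. The contamination argument behind the rule itself accepts that children in one household influence each other. That reasoning reached the allocation but not the stated analysis. When responses are positively correlated within clusters inside an arm, an analysis that treats the children as independent understates the variance of the arm means. Intervals are then too narrow and the test rejects too often.

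The second issue concerns entry. If a sibling is considered after the first child has been assigned, the second child's arm is already fixed and known, and minimization plays no part in choosing it. Eligibility leaves room for judgement: child and guardian must be clearly willing, and the investigator may exclude for other reasons. A decision to enter the second child could therefore depend on the arm.

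**Working it through.** **The plan's own figure.** The plan gives no figure for family clustering. Its sample size rests on independent children: difference 0.14, SD 0.28, two-sided alpha 0.05, power 85%, dropout 20%, total 164. These inputs give 2 × (0.28 × (1.960 + 1.036) / 0.14)² = 71.8, so 72 evaluable children per arm. Dividing by 0.80 gives 90 per arm and 180 in total, not 164. That mismatch is a separate matter and adds no weight to this point. It matters here only as the baseline for power: 82 × 0.80 = 65.6 evaluable per arm gives 81.7% power with no siblings.

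**Design effect.** Take an arm of n children. A share f are in sibling pairs, with intraclass correlation ρ for BMI z-score change, and no family has more than two participants. There are nf/2 pairs, and each adds 2ρσ² to the variance of the arm total. Hence

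Var(arm mean) = (σ²/n²) × (n + 2 × (nf/2) × ρ) = (σ²/n) × (1 + fρ), so DE = 1 + fρ.

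The true standard error is √DE times the one reported if families are ignored.

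**Type I error of the unadjusted test:** 2 × (1 − Φ(1.96/√DE)).

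**Power of a family-adjusted test:** Φ(0.14 / (0.28 × √(2 × DE / 65.6)) − 1.96).

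**Inputs not in the documents.** Both f and ρ are assumptions. The main range is f = 5% to 20% and ρ = 0.3 to 0.7. The first row below shows a still smaller share, and the third an intermediate case.

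| f | ρ | DE | True SE larger by | 1.96/√DE | True type I error | Power, family-adjusted | Second siblings among 164 (164 × f/2) |
|---|---|---|---|---|---|---|---|
| 2% | 0.3 | 1.006 | 0.3% | 1.954 | 5.1% | 81.5% | about 2 |
| 5% | 0.3 | 1.015 | 0.7% | 1.945 | 5.2% | 81.1% | about 4 |
| 10% | 0.5 | 1.05 | 2.5% | 1.913 | 5.6% | 79.8% | about 8 |
| 20% | 0.7 | 1.14 | 6.8% | 1.836 | 6.6% | 76.5% | about 16 |

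Over the main range, honest allowance for families costs 0.6 to 5.2 points of power (81.7 − 81.1 and 81.7 − 76.5).

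**Concealment.** No arithmetic applies; the statements have to be set side by side. Relatives must share an arm. Investigators who enrol receive the assignments, and families are not blinded. Recruitment lasts months, and nothing requires siblings to be entered together. It follows that a sibling entering after the family's first assignment would have a known arm. If all siblings are entered and assigned at one time, no such child exists. The last column of the table is the largest number of children this could affect under each assumption.

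**The case against.** The strongest reply has four parts.

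- **The analysis plan may add a family term.** A condensed article can leave the full random-effects structure to a document not shown here, and it does mention unspecified sensitivity analyses. A reader might infer that family clustering has been ruled out. The text does not say so; it is silent. What stands is that the article fixes a clustered allocation, names one source of correlation, and names tests that assume independence. Followed as written, these do not fit together.
- **The effect is small.** Both siblings must have obesity, be aged 8 to 11, be in grades 3 to 6, be willing and pass a long exclusion list. The relevant correlation is for change after adjustment for age, sex and baseline BMI z-score, which removes some family resemblance, and dietary plans are individual. This stands. The 6.6% figure needs both assumptions at their upper limits.
- **Concealment may be intact.** A reader might infer that later siblings' arms are known before enrolment as a matter of course, and that the concealment statement is therefore contradicted. The documents do not support that. They do not say that siblings enter in turn, and one child's arm reveals nothing about unrelated children. Only the conditional statement stands: if entry is staggered, concealment fails for that later child.
- **A family random intercept may be hard to fit.** With few pairs and mostly single children, its variance is weakly identified. This stands, and it favours clustered robust errors.

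**Conclusion.** The point holds in a limited form. The allocation rule makes families the unit for related children, and the stated analysis does not carry this through. If siblings take part and respond alike, standard errors are understated by a little and the nominal 5% test runs at 5.2% to 6.6%, most likely near the lower figure. This rests on an assumed share of children in pairs (5% to 20%), an assumed intraclass correlation (0.3 to 0.7) and at most two participants per family; none of these is in the documents. The loss of concealment is conditional on staggered entry, which the protocol neither states nor excludes. Nothing here threatens the trial, but the remedy is cheap enough that it should be adopted.

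**What to change.** 1. Record a family ID for every participant.
2. In the between-group mixed and logistic models, use family-clustered robust standard errors, or a family random intercept if it can be estimated. Let these models replace the unadjusted two-sample and chi-square tests for between-group comparisons.
3. Add a sensitivity analysis with one child per family: the first enrolled, or one chosen at random where siblings were assigned together.
4. State that consent and baseline are completed for all eligible siblings before a single family-level assignment.
5. Report how many siblings, if any, entered after their family's arm was known.

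Items 1 to 3 and 5 can still be adopted if recruitment is under way; item 4 then applies to families not yet assigned. The cost is one extra field on the case record form, slightly wider intervals, and an occasional short wait so that siblings can be enrolled together.
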